**Adverse Events**

AEs are defined as any untoward medical occurrence that develops during a clinical trial. An AE can be any unfavorable and unintended sign, symptom, or disease temporally associated with the use of a medicinal product, regardless of the relationship to the study drug. Each AE will be recorded on a separate adverse event case report form (CRF). Concomitant medications will be documented by generic name. Laboratory abnormalities will be described. Medications taken to relieve symptoms of the AE will also be recorded in addition to the outcome. AEs will be reported per the National Cancer Institute Common Terminology Criteria for Adverse Events (NCI CTCAE) version 3.0. The Principal Investigator will determine the severity of events and grade the event as follows:

**Grade 1:** Mild AE

**Grade 2:** Moderate AE

**Grade 3:** Severe AE

**Grade 4:** Life-threatening or disabling AE

**Grade 5:** Death related to AE

**Serious Adverse Events**

All serious AEs (SAEs) will be followed until resolution and/or until a cause is identified. SAEs include the following:

- Death
- A life-threatening adverse drug experience
- Inpatient hospitalization or prolongation of an existing hospitalization
- A persistent or significant disability/incapacity (defined as a substantial disruption of a person’s ability to conduct normal life functions)
- A congenital anomaly/birth defect
- An important medical event that (while it may not result in death, be life-threatening or require hospitalization) may jeopardize the patient and require medical or surgical intervention to prevent one of the outcomes listed in this definition

**Reporting Serious Adverse Events**

Any SAE occurring during the course of the study, considered drug related, will be reported by fax within 24 hours to the sponsor. In addition, these SAEs will be reported to the Duke Institutional Review Board (IRB) within a timely manner according to the IRB requirements. Study drug related SAEs will also be monitored by the Data Safety Monitor (DSM) throughout the study and reported to MedWatch. The DSM may at any point temporarily stop the study while he/she evaluates the impact of the SAE(s).

**DISCONTINUATION FROM STUDY**

The following occurrences shall result in the discontinuation of a patient from the clinical study:

- Patients who develop a Grade 4 or Grade 5 SAEs considered possibly, probably, or definitely to be related to study drug.
- Patients who decide not to participate further in the clinical study.
- If, in the investigator’s or clinician’s opinion, it is in the best interest of the patient to discontinue participation in the study.
- Patients in the active surveillance/preemptive therapy arm who are started on systemic antifungal therapy in the absence of a positive BDG test or without evidence a new proven or probable IFI by EORTC/MSG criteria.

All patients who withdraw or discontinue due to reasons other than withdrawal of consent will be followed for the endpoints of mortality at SICU and hospital discharge.

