**Standard care/empiric therapy group**

Patients in the standard care arm will also have biweekly blood draws for the BDG assay until ICU discharge, but the test will not be performed in real-time. Specimens collected from subjects in this arm of the study will be batched and tested retrospectively. The clinicians, therefore, will be blinded to the BDG results and can not use the assay to inform treatment decisions. Because BDG test characteristics in SICU patients are not known, an essential aspect of this study is our ability to assess test performance in the population of interest in an unbiased fashion. Patients in the standard care group may receive antifungal prophylaxis and/or treatment at any time based on the discretion of the treating physician.

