**Concomitant Medications**

There are no drugs that are contraindicated with anidulafungin. However, for study purposes, other systemic antifungal agents including amphotericin products, azoles, and/or investigational antifungal drugs may not be given during study drug dosing. If a patient in the preemptive therapy arm requires one of these agents, the patient must be discontinued from the study.

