**INITIATION OF PRE-EMPTIVE OR EMPIRIC THERAPY**

- APACHE II score recalculated based on laboratory and clinical features in preceding 24 hours (http://www.sfar.org/scores2/apache22.html).
- Complete physical examination including vital signs will be obtained within 72 hours of study drug initiation.
- Assess and document whether patient meets EORTC/MSG criteria for proven or probable IFI.
- Laboratory evaluation (LFTs will be obtained if not already done in preceding 3 days).
- Oral wash or ETS for semi-quantitative fungal culture with susceptibility testing will be performed.
- Supporting evidence of IFI obtained as part of routine care will be documented.
- Positive BDG test will prompt two sets of blood cultures to be obtained within 12 hours, if not already collected a part of routine care. Culture results will be made available for clinical care.
- Concomitant medications will be documented.
- AEs will be recorded.

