**Data Analysis**

Data Analysis will be performed after completion of data entry, database closure, and verification of database accuracy. All primary and secondary analyses will be performed on the intent-to-treat basis.

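### Off-strategy antifungal use removes patients from the study in the preemptive arm only, with only mortality named as later follow-up, which the intent-to-treat comparison of secondary endpoints cannot absorb

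*Protocol*

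**What the plan says.** **Preemptive arm.** Discontinuation from Study removes from the study those preemptive patients "who are started on systemic antifungal therapy in the absence of a positive BDG test or without evidence a new proven or probable IFI". Concomitant Medications bars other systemic antifungals during study-drug dosing and adds: "If a patient in the preemptive therapy arm requires one of these agents, the patient must be discontinued from the study".

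**Standard-care arm.** The same event has no such consequence: "Patients in the standard care group may receive antifungal prophylaxis and/or treatment at any time", at the treating physician's discretion.

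**After discontinuation.** Patients who leave for reasons other than consent withdrawal "will be followed for the endpoints of mortality at SICU and hospital discharge". The Censoring section repeats this and censors only consent withdrawals.

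**Analysis.** "All primary and secondary analyses will be performed on the intent-to-treat basis" (Data Analysis). The efficacy paragraph compares the proportions with invasive fungal infection (IFI) and invasive candidiasis (IC) by Fisher's exact test over the SICU stay. Nothing is imputed in the primary analysis, and dropouts are not replaced.

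**Text pointing to fuller follow-up.** The All Subjects section lists weekly IFI, adverse-event and antimicrobial records for the whole SICU stay. Follow-up (SICU Discharge) follows all study subjects to SICU discharge, with an IFI assessment there. Neither section says whether it covers a patient who has been discontinued.

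**The concern.** A clinician who starts an antifungal without a positive β-D-glucan (BDG) test usually does so because fungal infection is suspected. In standard care that patient stays under weekly assessment. In the preemptive arm the patient leaves the study and, as the discontinuation text reads, is promised only mortality follow-up. Any loss of data would therefore fall on one arm, and on patients chosen for a reason linked to the outcome.

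The exposed secondary endpoints are IFI and IC, febrile days, antifungal use, cost, breakthrough IFI and colonization. Antifungal use and cost need no assumption about infection risk. If recording stops, off-strategy treatment goes uncounted in the preemptive arm and is counted in full in standard care.

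The IFI comparison also has a use during the trial. Interim Analyses and Stopping Rules lets large differences in IFI prevalence lead to a recommendation to stop randomisation or redesign the trial, and the Data Safety Monitor section applies no statistical stopping rules. Endpoint data that were never collected cannot be recovered by analysis.

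**Working it through.** **1. The plan's own figures.** From Sample Size: 100 × 3/4 = 75 and 100 × 1/4 = 25. A 25% positive rate gives 0.25 × 75 = 18.75, rounded to 19 treated. All reproduce. There is no power calculation and no expected IFI rate to reproduce.

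**2. The passages side by side.**

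| | Preemptive arm | Standard care |
|---|---|---|
| Antifungal outside the strategy | Discontinued from the study | Allowed; stays in |
| IFI status when treatment starts | Documented (Initiation section) | Documented |
| Later follow-up named | Mortality at SICU and hospital discharge | All SICU assessments |
| Analysis | As randomised | As randomised |

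The third and fourth rows conflict. An endpoint not collected in part of one arm cannot be analysed as randomised when nothing is imputed.

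**3. Illustration of size.** All inputs here except the arm sizes are assumptions.

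- p = true IFI risk, 10% in both arms. The Introduction mentions 10% only as a background threshold for prophylaxis.
- d = share of the preemptive arm discontinued under the rule.
- r = share of those patients whose IFI first meets criteria after discontinuation and is not captured.
- Observed risk with discontinued patients kept as non-events: p − d·r.
- Observed risk with them dropped from the denominator: (p − d·r)/(1 − d).
- Expected true cases: 75 × 0.10 = 7.5.

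| d | r | IFIs unseen (75·d·r) | Kept as non-events (RR) | Dropped (RR) |
|---|---|---|---|---|
| 5% | 10% | 0.38 | 9.5% (0.95) | 10.0% (1.00) |
| 10% | 20% | 1.5 | 8.0% (0.80) | 8.9% (0.89) |
| 20% | 20% | 3.0 | 6.0% (0.60) | 7.5% (0.75) |
| 20% | 30% | 4.5 | 4.0% (0.40) | 5.0% (0.50) |

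For the second row: 0.10 − 0.10 × 0.20 = 0.08, and 0.08/0.90 = 0.089. If IFI is still captured to SICU discharge in everyone, the contrast is 10% against 10% and the risk ratio is 1.00. If discontinued patients are dropped and r equals the overall 10%, there is no bias either.

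**4. Effect on the test.** Exact enumeration of the two-sided 5% Fisher test, 75 against 25, with no true difference, gives these chances of a result favouring the preemptive arm: 2.2% with full capture, 4.7% at an observed 8%, 9.5% at 6% and 18.6% at 4%. The distortion is mainly in the estimate.

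**5. The opposing influence.** "Positive BDG test will prompt two sets of blood cultures to be obtained within 12 hours" can act only in the preemptive arm, because standard-care samples are batch-tested at the end of the study. Extra cultures find more IC in that arm. The documents give no basis for sizing this, and the table leaves it out.

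**The case against.** **Non-collection is not stated.** A reader might infer that all data except mortality cease at discontinuation. No section says so. Mortality is named without the word *only*, the All Subjects and Follow-up sections speak of all study subjects, and only consent withdrawals are censored. SICU stay should survive in any case, since mortality at SICU discharge cannot be recorded without knowing when the patient left. Serious adverse events are followed to resolution or until a cause is identified. This stands in part: the loss is an inference. But Follow-up (SICU Discharge) already includes mortality at both time points, so if it covered discontinued patients, the separate mortality sentences would add nothing. The sections need reconciling on either reading.

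**Test-negative infections are not all lost.** A reader might take the 81% sensitivity behind the BDG cut-off and conclude that the remaining 19% of infections disappear. The documents do not support that. IFI status is documented when treatment starts, so a patient already meeting criteria is counted; only infections meeting criteria later are at risk. The 81% also concerns IC rather than IFI.

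**The direction is not fixed.** A reader might infer that an ineffective strategy will appear to prevent IFI. Triggered cultures push the other way, so this is not established.

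**The primary endpoints are largely untouched.** Test performance uses the standard-care arm, and feasibility counts these very withdrawals. IFI is secondary, the trial is not powered for efficacy, and the interim section itself expects too few patients for significance on it. This stands and limits the severity.

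**The *or* looks like a drafting slip.** The feasibility sections describe withdrawal for antifungals started without a positive test. That indicates the intent but does not remove the conflict. Read literally, the rule also discontinues a BDG-positive patient without proven or probable IFI who starts the preemptive therapy described in the active surveillance section.

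**Conclusion.** The point holds in conditional form. The one-arm discontinuation is explicit. Naming only mortality afterwards conflicts with intent-to-treat analysis of all secondary endpoints and sits unclearly with follow-up of all subjects to SICU discharge. If other assessments stop, infections first meeting criteria after discontinuation, and later fever, antifungal use and cost, go uncounted in the preemptive arm alone.

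The size cannot be derived from the documents. The illustrative risk ratios of 0.80 and 0.60 rest on an assumed 10% risk, on 10% or 20% discontinued with 20% later IFI, and on counting discontinued patients as non-events. They move toward 1 if those patients are dropped (0.89 and 0.75) and equal 1 if IFI is still captured. The net direction is uncertain because of the triggered cultures.

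Severity is moderate: the endpoints affected are secondary in an unpowered feasibility trial, but IFI differences may inform interim recommendations.

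**What to change.** In Concomitant Medications, Discontinuation from Study and Censoring, separate departure from the assigned strategy from leaving the study:

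- State that every randomised patient who has not withdrawn consent keeps all SICU assessments (IFI, adverse events, fever, antifungal use, stay) to SICU discharge and is analysed in the assigned arm. Make All Subjects and Follow-up (SICU Discharge) say the same.
- Record off-strategy antifungal use as a feasibility outcome, which the feasibility sections already intend.
- Reconcile the *or* wording with the active surveillance section and the two feasibility sections. Which treatment rule applies is for the investigators to settle; the change proposed here concerns data collection and analysis only.

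An IC analysis leaving out cases found on triggered cultures should not be part of this fix. It would remove events from one arm after randomisation, which is the kind of selection at issue.

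The cost is protocol wording and a little more record abstraction, from records already reviewed weekly. The small downside is that some follow-up will be off-strategy, as intent-to-treat analysis accepts.

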**DATA SAFETY MONITOR**

A DSM consisting of an Infectious Diseases physician will review the study every 4 months. The DSM can recommend early terminations to assure the safety of study participants or for efficacy in order to limit the number of patients monitored by a strategy that is less effective. However, specific statistical stopping rules will not be applied. The DSM will make recommendations regarding adaptations to the study if needed after the review of interim analysis results.

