**STATISTICAL METHODOLOGY**

**Sample Size**

Targeted enrollment is 100 adult SICU patients. This study will not be powered to show a difference in the efficacy of preemptive management versus standard care due to single center population constraints in addition to cost limitations. Sample size calculations were therefore based on the number of adult patients expected to be admitted to the SICU over a 1 year period who are likely to meet inclusion criteria (n=700). Based on prior experience, it is reasonable to expect an accrual of 100 patients in a year. Using a 3:1 randomization strategy, 75 will be assigned to active surveillance and 25 to standard care. We estimate that 25% of patients will develop a positive test(13;25;27) and 19 will receive anidulafungin. These numbers should provide sufficient data for a preliminary feasibility evaluation of the preemptive strategy.

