**Statistical Analyses**

Statistical analysis will be performed using SAS software. P values and 95% confidence intervals will be 2-tailed and statistical significance set at the 5% level unless otherwise specified.

*Demographics and Baseline Characteristics*

Demographic and baseline characteristic information will be summarized and compared using the Chi-squared test for discrete variables and one way ANOVA for continuous various to assess any imbalance between treatment groups.

*β-D-glucan Test Characteristics*

β-D-glucan test characteristics, using data collected from standard care group, will be described using sensitivity, specificity, positive and negative predictive values. Proven and probable cases of IFI, as defined by EORTC/MSG criteria (**tables 3 and 4**), will constitute the standard for comparison.

*Feasibility Analysis*

Feasibility will be a description of preemptive protocol adherence, BDG test requests off schedule, and the number of patients withdrawn from the preemptive arm due to the initiation of empiric systemic antifungal therapy in the absence of a positive BDG test.

*Efficacy End-Points*

Development of IFI during the study period will be assessed by the principal investigator (PI) and a second blinded investigator using predefined EORTC/MSG criteria for proven or probable disease. The study period is defined as the time the patient was cared for in the SICU. The proportions of patients developing IFI, and IC specifically, in each group will be compared using Fisher’s exact test. The median ICU stay and number of febrile days while in the ICU will be compared using the Kruskal-Wallis test. Patient mortality, overall and attributed to IFI, will also be summarized by group. Response-to-therapy (RTT) will be determined by the PI and a blinded second investigator. The RTT population will consist of all patients who were underwent BDG monitoring for at least 3 days and received at least 1 dose of systemic antifungal therapy.

*RNA Analyses*

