**INTERIM ANALYSES AND STOPPING RULES**

The planned interim analysis of key safety and endpoint data will be performed by the DMC every 4 months. It is unlikely that there will be a sufficient numbers of patients to claim statistically significant differences for the secondary IFI or mortality endpoints. The primary objective of these analyses will be to view the data for safety outcomes and to look for differences in mortality and the development of IFI between the 2 arms. Other objectives are to review patient recruitment, compliance with study protocol submission of data forms, and other factors that reflect study progress. If significantly large and important differences are observed in mortality or IFI prevalence between the 2 arms, the DMC may recommend the randomization of patients be stopped, or if the difference observed is indicative of efficacy, the design and conduct of the trial may be modified to recruit more patients and to design the trial to evaluate differences in mortality between the 2 arms.

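### The monitor may recommend stopping for efficacy or enlarging into a mortality trial after 4-monthly between-arm looks, with no statistical boundary and two sections that conflict

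*Protocol*

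**What the plan says.** Protocol, Data Safety Monitor: one infectious diseases physician reviews the study every 4 months and may recommend early termination for safety "or for efficacy in order to limit the number of patients monitored by a strategy that is less effective". The section then states that "specific statistical stopping rules will not be applied", and allows recommended adaptations once interim results have been seen.

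Protocol, Interim Analyses and Stopping Rules: "The planned interim analysis of key safety and endpoint data will be performed by the DMC every 4 months". The purpose is safety and also to "look for differences in mortality and the development of IFI between the 2 arms". If differences in mortality or invasive fungal infection (IFI) are large and important, the committee may recommend that randomization stop. Alternatively, "if the difference observed is indicative of efficacy, the design and conduct of the trial may be modified to recruit more patients" and to evaluate mortality. No trigger, added sample size or rule on the patients already enrolled is given. The same section concedes that significant differences on these endpoints are unlikely.

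Protocol, Statistical Analyses: "P values and 95% confidence intervals will be 2-tailed and statistical significance set at the 5% level unless otherwise specified". No allowance is made for repeated looks. IFI and invasive candidiasis are compared by Fisher's exact test. Mortality is summarized by group and no test is named.

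Protocol, Sample Size: 75 and 25 patients, no power claimed for efficacy, and "it is reasonable to expect an accrual of 100 patients in a year".

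**The concern.** A protocol may leave the details of a boundary to a statistical analysis plan. This one does not: it rules a boundary out, so a later plan that supplied one would contradict it. The protocol still creates two routes by which a between-arm difference in a secondary, unpowered endpoint can change the trial, namely stopping and enlargement.

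Three things are at stake.

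- A nominally significant difference at an interim look could be reported at a 5% level that it does not have.
- A stop on a chance difference would cost the primary aims. β-D-glucan (BDG) test performance is estimated in the standard care arm only, and few patients are expected to receive anidulafungin.
- The two sections give different instructions for the same signal. Under Data Safety Monitor, efficacy is a ground for ending the trial. Under Interim Analyses and Stopping Rules, it is a ground for recruiting more patients.

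**Working it through.** **Inputs from the protocol.** 100 patients in about a year, 3:1 allocation, reviews every 4 months, two-sided 5%, Fisher's exact test. **Assumptions.** The protocol gives no event rates for this population, so 5-10% is used for IFI and 20-30% for mortality. The 15-point and 10-point differences below are illustrative, because the protocol sets no numerical trigger.

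**Step 1: the plan's own figures.** 100 × 3/4 = 75; 100 × 1/4 = 25; 0.25 × 75 = 18.75, rounded to 19 treated. These reproduce. No interim error rate is stated.

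**Step 2: the looks.** 12 / 4 = 3 analyses, at about 33, 67 and 100 patients, or 25:8, 50:17 and 75:25.

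**Step 3: unadjusted testing, no true difference (simulation, Fisher p<0.05).** Ranges cover repeated runs.

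| Event rate | Any of 3 looks | Final look only |
|---|---|---|
| 30% | 7.4-7.5% | 3.7-3.8% |
| 20% | 6.1-6.5% | 3.2-3.5% |
| 10% | 4.4-4.8% | about 2.6% |
| 5% | 3.0-3.1% | about 2.2% |

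The large-sample value for three unadjusted looks is 10.7%. Fisher's conservatism at these sizes keeps the actual figure lower. Since no test is named for mortality, note that an uncorrected chi-square test would give 10.0% and 11.1% at event rates of 20% and 30% (looks at 25:8, 50:16 and 75:25).

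**Step 4: chance differences of 15 points or more at look 1 or 2, no true difference.**

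| Event rate | Either direction | Favouring preemptive therapy |
|---|---|---|
| 30% | 52% | 25% |
| 20% | 44% | 21% |
| 10% | 25% | about 13% |

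With 8 controls, one patient is 1/8 = 12.5 points.

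**Step 5: what a stop would cost.** At look 1 there would be 8 controls instead of 25 for BDG performance, and about 0.25 × 25 = 6 treated patients instead of 19. At look 2 there would be 17 controls and about 0.25 × 50 = 12 or 13 treated.

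**Step 6: enlargement.** Suppose the trial is extended by a fixed 100-300 patients after a favourable final difference of 10 points or more, and only the pooled data are tested at one-sided 2.5%.

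- Probability of extending: 14% at 20% mortality, 17% at 30%.
- Error among extended trials: 9-15%.
- Unconditional error is the product of the two. For example, 0.14 × 0.15 = 2.1% (20% mortality, 100 added) and 0.17 × 0.09 = 1.5% (30% mortality, 300 added). Across the scenarios it is about 1.5-2.3%, below 2.5%.

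The level is exceeded in two other cases:

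- A claim may rest on either a significant look or the pooled test: one-sided error 5.3-6.5%. This is a large-sample figure for three looks, a trigger of z from 1 to 1.96, and added patients of 1 to 9 times the pilot. Most of it comes from the looks.
- The added size is chosen freely from the interim result: worst case α + exp(−z²/2)/4 = 0.025 + exp(−1.96²/2)/4 = 0.025 + 0.037 = 6.2%.

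**Step 7: effect of a boundary.** Fisher p<0.001 at the two interim looks and p<0.05 at the end gives 3.8% at a 30% event rate, essentially the final-look-only value. The large-sample equivalent is 5.04%.

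**The case against.** The strongest reply is that this is a one-year, open-label pilot of 100 patients. Its primary endpoints are feasibility, test performance and safety. IFI and mortality are secondary, efficacy power is disclaimed, and the protocol itself warns that significance is unlikely. Informal monitoring is common in such a trial, and the monitor only recommends. All of this stands and limits the severity. It would settle the matter if the looks were confined to safety and conduct, but both monitoring sections go further.

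Four stronger readings are tempting, and the documents do not support them.

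- **That a pooled mortality test would run at 9-15% error.** That range applies only among trials already selected for a favourable trend. The level of a test is unconditional, and for a fixed extension tested once it stays below 2.5%. The protocol also plans no pooled test; it merely fails to exclude one.
- **That half of all trials would stop falsely for benefit.** The 52% counts both directions against an assumed 15-point threshold, at a 30% event rate. The protocol asks for large and important differences and gives no number. The figure measures noise and does not predict what a monitor would do.
- **That the IFI comparison breaches 5%.** With Fisher's test at 10% or less, it does not.
- **That the monitor can itself stop or enlarge the trial.** The text grants a power to recommend.

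**Conclusion.** The point holds, with modest severity. The protocol authorises recommendations to stop for efficacy or to enlarge on repeated between-arm comparisons, refuses a boundary, keeps the 5% level, and gives conflicting consequences for the same signal.

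For mortality-like event rates, unadjusted Fisher testing roughly doubles the chance of a false significant result compared with the final look alone, and takes it moderately above 5%. The larger practical risk is that a chance difference among 8 or 17 controls ends a study whose primary aims need all 25 controls and about 19 treated patients.

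Enlargement by a fixed number with a single pooled test is not in itself a breach. The level is at risk if a claim may also rest on an interim look, or if the added size depends on the interim result, and the protocol rules out neither.

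These conclusions rest on three equally spaced looks and on the assumed event rates; slower accrual would add looks.

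**What to change.** In both Data Safety Monitor and Interim Analyses and Stopping Rules:

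1. Limit the 4-monthly reviews to safety, harm and conduct, and delete stopping for efficacy. If efficacy stopping is kept, set a fixed extreme boundary at the interim looks, for example Fisher p<0.001 on mortality.
2. State that interim comparisons support no efficacy claim.
3. State that any mortality trial is a new stage whose confirmatory analysis either excludes the pilot patients or combines them by a method specified in advance.
4. Reconcile the two sections so that an efficacy signal has one stated consequence. Name one reviewing body at the same time: it is a single monitor in one section, a committee in the other and a board in the synopsis.

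The cost is protocol wording. The sponsor gives up an informal option to stop early for benefit and the free re-use of up to 100 pilot patients if the trial is enlarged. An interim boundary of p<0.001 leaves the overall error rate essentially unchanged.
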